#### The Child and Adolescent Scale of Participation (CASP)

The CASP measures participation of children with an ABI in home, school and community activities compared to typically developing children of the same age as reported by parents or guardians [140, 142]. Like the CASE, the CASP was developed as part of the CFFS to monitor outcomes and needs of children with an ABI. The CASP consists of 20 ordinal scaled items in four subsections: 1) Home participation, 2) Community participation, 3) School participation, and 4) Home and community living activities. The 20 items are rated on a four-point scale: “Age Expected (Full participation),” “Somewhat Restricted,” “Very Restricted,” “Unable”. A “Not Applicable” response can be selected when the item reflects an activity that the child would not be expected to participate in due to age (e.g. work). The CASP also includes open-ended questions that ask about effective strategies and supports and barriers that affect participation. The CASP takes about 10 min to administer and no specific training is needed.

The CASP has reported evidence of test re-test reliability (ICC = 0.94), internal consistency (α ≥ 0.96) and construct and discriminant validity. Moderate correlations were found between the CASP scores and scores from measures of functional activity performance on the PEDI (r = 0.51–0.75), extent of child impairment on the Child and Adolescent Factors Inventory [CAFI (r = −0.58 to −0.66) and problems in the physical and social environment as measured by the CASE (r = −0.43 to −0.57) [140, 142, 143]. Significant differences in CASP scores were found related to type of disability [142]. Children without disabilities, on average, had significantly higher CASP scores than children with disabilities. No significant differences were found related to age category [142]. The CASP will be available for parents and/or guardians to fill out in paper or online format.

#### Participation and Environment Measure for Children and Youth (PEM-CY)

This parent-report instrument examines the frequency and level of participation in home, school and community settings [144]. In addition, the measure also addresses whether the surrounding environment makes it easier or harder to participate. There are 10 items in the home section, five in the school section and 10 in the community setting. For each item, the parent is asked to identify how frequently (over the past four months) the child has participated (eight options: daily to never); how involved the child typically is while participating (five point scale: very involved to minimally involved); and whether the parent would like to see the child’s participation in this type of activity change (no or yes, with five options for the type of change desired). After each section the parent is then asked to report on whether certain feature of the environmental makes it easier or harder for the child to participate. The PEM-CY has reported moderate to good internal consistency (0.59 and above) and test-retest reliability (0.58 and above) in a population of children (aged 5 to 17 years) with and without disabilities residing in the United States of America and Canada (*n* = 576) [144]. The PEM-CY will be collected at baseline using either paper or online questionnaire format to gain an understanding of the participation of children and adolescents and the impact of environmental support.

#### Strengths and Difficulties Questionnaire (SDQ)

The Strengths and Difficulties Questionnaire (SDQ) [145, 146] is a 33 item parent-rated questionnaire that is used to assess parents’ perceptions of pro-social and difficult behaviours in their child. Parents are required to respond to 25 questions about their child’s behaviour in the last six-months using a three-point likert scale (i.e., “0” = not true to “2” = certainly true). These 25 questions combine to create five sub-scales of: frequency of emotional symptoms; conduct problems; inattention/hyperactivity; peer problems; and prosocial behaviour (e.g. “considerate of other people’s feelings”). A total score for each scale (0–10) and overall total difficulties score (0–40) will be calculated, with higher scores indicating more distress on all scales except prosocial behaviour. Scores of 17 or above for the total difficulties scale will be used a clinical cut-off point. Scores from the five sub-scales and the overall difficulties scale will be used as a measure of the child’s psychological functioning. The overall total difficulties score has been demonstrated to have moderate to high internal consistency (α = 0.73–0.82) and test-retest reliability (*r* = 0.77–0.85) [147].

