### Secondary hypotheses

Compared to usual care, Mitii™ training will achieve significantly greater:Upper limb activity (unimanual and bimanual), as measured on the Jebsen-Taylor Test of Hand Function (JTTHF), MUUL and the Assisting Hand Assessment (AHA) [56];Lower limb gross motor capacity assessed using the Timed Up and Go (TUG) test, 6-min Walk Test (6MWT) and the High-Level Mobility Assessment Tool (HiMAT);Habitual physical activity (as measured on the ActiGraph® accelerometer) [57];Neurovascular (functional MRI) changes;Visual perception (visual discrimination, visual memory and visual sequential memory) measured on the Test of Visual Perception Skills (TVPS) [58];Executive functioning including information processing, attentional control, cognitive flexibility, goal setting, working memory and behavioural manifestations in everyday life as measured by subtests from the Delis-Kaplan Executive Function System (D-KEFS), the Wechsler Intelligence Scale for Children Fourth Edition (WISC-IV), the Comprehensive Trail Making Test (CTMT), Tower of London – Second Edition and the Behaviour Rating Inventory of Executive Function (BRIEF);Attention including performance on tasks of attention (TEA-Ch) and attention in everyday life as measured by parent rating (Conner’s 3);Psychological functioning as measured by the Strengths and Difficulties Questionnaire (SDQ);Performance and satisfaction with occupational performance goals using the COPM;Participation as measured by the Child and Adolescent Scale of Environment (CASE) and Child and Adolescent Scale of Participation (CASP);QOL on the domains of functioning and participation as measured on the Kidscreen-52;Parent reported functional abilities in self-care and daily activities (using the MobQues28) [59]

Finally, Mitii™ will be more cost-effective compared with usual care as shown by resource use and consequence based on function (AMPS) and QOL (Child Health Utility 9D (CHU-9D) [60] and Kidscreen-52 [61])

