### Study procedure

To account for children’s varying abilities to attend and concentrate and, to mitigate fatigue the following scheduling strategies will be used to maximise data integrity during baseline and follow up assessments. Families will be contacted prior to baseline assessments to ascertain whether they feel their child will need one or two days to complete assessments. All participants will attend The University of Queensland, St Lucia campus for all assessments, minimising travel. Neuropsychological testing will be scheduled first as this requires most attention and concentration by participants. Regular breaks will be scheduled for participants between assessments as necessary at baseline and follow-up appointments. All primary outcome clinical assessments will be performed prior to Magnetic Resonance Imaging (MRI). Extra time will be allocated at the start and end of each day to manage any unforeseen complications which may arise (e.g. travel/time delays and fatigue issues). Participants in the immediate intervention group will spend an additional day for Mitii™ training and return home with Mitii™ equipment to begin the 20 weeks intervention. After baseline assessments (T0), the waitlist group will continue care as usual for 20 weeks. All participants will then return to The University of Queensland after 20 weeks for a one to two day re-assessment (T1). The waitlist group will spend an additional day for Mitii™ training before returning home with equipment to commence the intervention. For each participant data will be collected at Baseline (T0). The immediate intervention group will have follow up assessments conducted immediately post-training at 20 weeks (T1) and retention at 40 weeks post-baseline assessments (T2). The waitlist group will have a second baseline assessment at 20 weeks (T1), post-intervention at 40 weeks (T2) and retention of effects at 60 weeks post-baseline assessments (T3).

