### Statistical analysis

Analysis will follow standard principles for RCTs. Primary and secondary outcomes will be assessed using two-group comparisons on all participants with evaluable data at 20 week follow-up assessments on an intention-to-treat basis. Statistical significance will be set at *p* < 0.05 for primary outcomes. Statistical significance for secondary outcomes will be defined separately for each suite of analyses prior to analyses being undertaken. Each significance level will be set to account for both type I and type II error rates due to the number of multiple comparisons. Validity of results will be checked using baseline and general descriptive information available for all eligible families. This includes comparing the key characteristics of families who completed the study with those who enrolled in the study but did not complete, and those who did not enrol. The primary outcome measures immediately post-intervention at 20 weeks will be AMPS and rep_max_ of functional strength exercises. Outcomes between treatment groups will be compared at follow-up using linear regression models, where treatment group (intervention or waitlist) and baseline score will be entered in as main effects. Secondary analyses will compare the outcomes between groups for physical activity, participation (CASE and CASP) and QOL (domains of Kidscreen-52).

For reproducibility studies (AMPS, physical activity capacity and performance measures and attention and executive functioning measures), units of variance will be assessed using an analysis of variance (ANOVA) model with Bland Altman Plots with 95 % limits of agreement (LOA). Intra-class correlation coefficients (model: 2-way mixed effects with absolute agreement) and 95 % confidence intervals will be calculated and interpreted as greater than 0.75 as excellent correlation, between 0.4 and 0.75 as adequate and less than 0.40, poor correlation [154]. The SEM will be calculated using [155]:$$ SEM= Standard\  Deviation\ (SD) \times \sqrt{\Big(1-ICC}\Big) $$

The MDC will be calculated using [155]:$$ MDC=SEM \times 1.96 \times \sqrt{2} $$

For attention and executive functioning measures, reliable change indexes (RCI) will be calculated using [156]:$$ RCI=\left( retestscore - initialscore\right)\div \left( standard\  error\  of\  difference,\  SDiff\right) $$

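### The SDQ's six-month recall is longer than the 20-week trial phase, so about six weeks of the rating compared at 20 weeks precede baseline in both arms

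*Protocol article*

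**What the plan says.** The Secondary hypotheses section of the protocol article expects Mitii to do better than usual care on "Psychological functioning as measured by the Strengths and Difficulties Questionnaire (SDQ"; no other instrument is named for that hypothesis. The SDQ section says that parents rate the child's "behaviour in the last six-months using a three-point likert scale", and that "Scores from the five sub-scales and the overall difficulties scale will be used as a measure of the child’s psychological functioning".

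The Statistical analysis section fixes the time of the comparison: "Primary and secondary outcomes will be assessed using two-group comparisons on all participants with evaluable data at 20 week follow-up assessments". It also puts the baseline score into the regression model beside treatment group.

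The Study procedure section sets the visits. The immediate group has "follow up assessments conducted immediately post-training at 20 weeks (T1", followed by "retention at 40 weeks post-baseline assessments (T2". For the other arm, "The waitlist group will have a second baseline assessment at 20 weeks (T1", with a post-intervention visit at week 40 and a retention visit at week 60. The Design section gives each phase, training or usual care, a length of 20 weeks.

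The article nowhere gives a shorter SDQ recall period for follow-up and does not mention that the recall period exceeds the interval between visits.

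**The concern.** The 20-week comparison is meant to show how children are doing after 20 weeks of Mitii compared with 20 weeks of usual care. A parent who follows the SDQ instruction at T1 rates a period that began before the child entered the trial. In those early weeks the arms cannot differ because of treatment, so any weight given to them shrinks the difference that the comparison is looking for.

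What is at stake is sensitivity. A real effect on behaviour would appear smaller than it is, on the only instrument named for this hypothesis. Once the ratings are collected, no analysis can split a single six-month rating into its weeks. The remedy therefore lies in the questionnaire wording and cannot be left to the analysis.

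**Working it through.** The plan gives no effect size, power or sample size for the SDQ, so there is no figure of its own to reproduce. The check is interval arithmetic.

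**Inputs**
- Recall period R: six months (SDQ section), about 26 weeks. Range tried: 24 weeks (six four-week months) to 27 weeks.
- Phase length and visit spacing: 20 weeks (Design and Study procedure).
- Time of the between-group comparison: week 20 (Statistical analysis).

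**Window at T1.** The rating at week t covers weeks t − R to t. At T1 this is 20 − 26 = −6 to week 20. Time before baseline = R − 20:

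| Six months counted as | Weeks before baseline | Share of window |
|---|---|---|
| 24 weeks | 4 | 4/24 = 17% |
| 26 weeks | 6 | 6/26 = 23% |
| 27 weeks | 7 | 7/27 = 26% |

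The overlap exists under each convention and is the same in both arms.

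**Possible dilution at T1.** Let w be the weight that a parent gives to the pre-baseline weeks, and suppose the effect is constant from the first day of training. The difference shown is then (1 − w) times the true effect. With even weighting, w = 6/26 and 20/26 = 77% shows (20/24 = 83% to 20/27 = 74% over the range above). If parents ignore the early weeks, w = 0 and nothing is lost. The protocol does not say how parents weight the period, so 77% is an illustration.

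**Baseline adjustment.** The T0 rating covers weeks −26 to 0 and the T1 rating weeks −6 to 20, so the two share weeks −6 to 0. Adjusting for the T0 score does not restore the contrast lost at T1, because the T1 rating itself still contains those weeks.

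**Later visits, if the SDQ is collected then (26-week window)**
- T2, week 40: weeks 14 to 40. In the immediate group the retention rating includes the last 6 weeks of training. In the waitlist group the post-intervention rating includes the last 6 weeks of usual care.
- T3, week 60, waitlist group only: weeks 34 to 60, which includes the last 6 weeks of training.

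**The case against.** The strongest reply is that the comparison remains fair. At T1 the same pre-baseline weeks enter both randomised arms, and the whole 20-week contrast lies inside both windows. That is correct. A reader might infer that the SDQ result is biased, but the documents do not support this; the only harm is possible dilution.

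Second, the size of the loss rests on assumptions. Nothing in the article shows that parents average evenly over 26 weeks, and they may lean towards recent behaviour. This stands. A reader might go further and assume that the effect builds linearly from zero over 20 weeks, so that the rating shows only (20 × 0.5)/26 = 38% of the end-of-training effect. That adds a second unsupported assumption, and most of the loss has another source. A recall of exactly 20 weeks, with no overlap at all, would show only (20 × 0.5)/20 = 50% under the same assumption. The 38% should not be used as the size of this problem.

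Third, the text shown has no instrument-by-visit schedule for the SDQ, no SDQ retention hypothesis, and no two-group comparison other than at 20 weeks. A reader might infer that the trial cannot separate retention from the effect during training. That is too strong: collection of the SDQ at T2 and T3 is only implied by the general visit plan, and 20 of the 26 weeks in a retention window would follow training.

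Fourth, other instruments touch related ground: the Conners 3 (aggression, hyperactivity/impulsivity, peer relations), the BRIEF (inhibition, emotional control) and the Kidscreen-52 (psychological well-being, moods and emotions). An effect on behaviour would not necessarily go unseen in the trial. None of them, however, is named for the psychological functioning hypothesis.

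Last, keeping the SDQ as described preserves the quoted cut-off and reliability figures. That is a real trade-off, and it is counted as a cost of the change. It does not remove the mismatch between recall period and phase length.

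**Conclusion.** The point holds in a limited form. The stated recall period and the stated visit spacing do not fit together: about 6 of 26 weeks in the T1 window precede baseline (4 of 24 to 7 of 27, depending on how six months is counted). This follows from the article's own figures.

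The consequence is possible dilution of the 20-week difference on one secondary questionnaire. Under even weighting and a constant effect about 77% of the effect would show; the true loss could be smaller, or nil if parents report only recent behaviour.

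For T2 and T3 the conclusion is conditional. If the SDQ is collected then, the scores span two phases and should not be read as pure post-training or retention effects.

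Neither the primary outcomes nor the sample size depends on the SDQ. The change is worth making because it is cheap before data collection and no analysis can replace it afterwards.

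**What to change.** For the SDQ as a trial outcome, use one recall period shorter than 20 weeks, for example the last month, worded identically at T0 and at every follow-up at which it is collected. Identical wording matters because the T0 score is the baseline covariate in the regression model. If the cut-off of 17 is wanted to describe the sample, also collect the six-month version at T0. State at which visits the SDQ is completed.

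If the wording cannot be changed, say in the protocol that the T1 score includes about six weeks before baseline, and that any T2 or T3 scores include about six weeks of the preceding phase.

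The cost is a changed instruction line, plus a second short parent form at T0 if the cut-off is kept. The quoted cut-off and reliability figures would not strictly apply to the shorter-recall scores.

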### Quality of Life

#### Kidscreen-52

The Kidscreen-52 is a generic measure of QOL which will be used to compare parents report of QOL for children with ABI compared to their age, gender and matched pair. The Kidscreen-52 has been described as the most useful generic measure of QOL of children as it addresses the multidimensional construct of QOL through various domains and focuses specifically on the well-being of children. It was developed to implement the views of children, through focus group work of 22,110 children [148]. The Kidscreen-52 Questionnaire takes 15–20 min to complete and consists of 52 questions across 10 domains: Physical Well-being; Psychological Well-being; Moods and Emotions; Self-Perception; Autonomy; Parent Relations and Home Life; Social Support and Peers; School Environment; Social Acceptance (Bullying); and Financial Resources. The items use a five point Likert-type scale to assess either the frequency of certain behaviours/feelings or, in a small number of cases, the intensity of attitude. Higher scores on the Kidscreen-52 indicate better health-related QOL and well-being. During development of this measure, a child self-report was administered for children 8–18 years old and a parent proxy version was administered for parents of children 5–18 years. Children below the age of eight were unable to self-report as their reports were likely to be unreliable. Reliability was calculated by Cronbach’s Alphas and ranged between 0.76 and 0.89 throughout the 10 domains of health-related QOL. Convergent and discriminant validity were tested using information of child’s physical and mental health. Correlations of up to 0.55 were found when correlating the Kidscreen-52 dimensions with frequency of physical complaints [148].

#### CHU-9D

The Child Health Utility (CHU-9D) will be used to measure participant QOL (parent/proxy completion). This relatively new instrument is specifically designed to measure health-related QOL in children and those affected by a disability from a young age [149]. It contains nine domains: worried, sad, pain, tired, annoyed, school/homework, sleep, daily routine and able to join activities. Each domain has five response levels. The CHU-9D is scored on a scale of 0–100 using preference weights which allow the calculation of Quality Adjusted Life years (QALYs) for use in economic evaluation. Preference weights are available from a general adult United Kingdom population and from an Australian population of 11–17 year old adolescents [150, 151].

### Environmental and personal factors

The same study questionnaire which was used for a previous Mitii™ protocol will be used [89]. This questionnaire was developed to capture important demographic information that has been shown in the literature to influence participation. Information includes family ethnicity, household income, socio-economic status, family structure and supports, and family interests. The questionnaire will be administered at baseline. A measure of social advantage/disadvantage will also be derived from postcode of residence using the Index of Relative Socio-economic Advantage/Disadvantage (2006) from the Australian Bureau of Statistics [152]. Deciles will be reported on a continuum with lower scores reflecting greater socio-economic disadvantage and higher scores reflecting socio-economic advantage.

### Exit interview

An exit interview will be conducted with participants and their parents or guardians to investigate engagement in web-based therapy in the home environment to guide future clinical implementation. Semi-structured interviews will be conducted by a therapist who is not involved in the conduct of the study, audio recorded and transcribed verbatim until saturation of data is achieved. Transcripts will be analysed using an inductive approach.

### Healthcare costs

Virtual trainers will keep a diary to document the amount of time taken to monitor and progress programs, contact families and troubleshoot any technical difficulties. These data will be used to estimate the costs associated of the Mitii™ program. A cost will be assigned to each resource; allied health visits by state health wage rates; medical care and diagnostic/investigational services according to the fees in the national Medicare Benefits Schedule [153].

## Statistical analysis

### Sample size

The primary basis for sample size calculation for this study is adequate power (80 %) to detect a clinically important difference for the comparison between the functional effects of Mitii™ (as measured on the AMPS and rep_max_ of functional strength exercises) and usual care at the primary endpoint (20 weeks). This study examines a continuous response variable from matched pairs, waitlist control and immediate-intervention participants with one waitlist control per immediate intervention participant.

In a previous study of Mitii™ in children with unilateral CP (n = 102) the response within each group was normally distributed with SD 0.40 on the AMPS process subscales [49]. To detect a real changes in ADL processing abilities (0.30 units of greater) [92] between groups with 80 % power and α = 0.05, 29 children from each group are required to complete 20 week follow-up assessments.

For rep_max_ of functional strength exercises in a previous reliability study, the response within each subject group was normally distributed with a SD of five sit-to-stand repetitions [93]. If the clinically important difference between groups is four repetitions we will need 26 children from each group to complete 20 week follow-up assessments with, α = 0.05 [47].

Based on a previous RCT using 3T fMRI there were activation in the representative cortex for motor studies with good signal to noise ratio. Participant numbers will allow for some loss of information due to participant refusal (10 %) and scans where motion is a confounder (10 %). To detect fMRI changes between baseline to follow-up assessment (20 weeks) with 80 % power and a SD of 0.65, we will require 39 participants. If the supplementary motor area (SMA) is considered, given coefficients of variation (COV) for control subjects performing motor tasks (COV of 11 % in PM1 and 35 % in SMA, and activation signal of 1.5 %, we will be able to detect differences in percentage activation levels over time as small as 0.47.

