**Methods/Design:**

Sixty independently ambulant children (30 in each group) at least 12 months post ABI will be recruited to participate in this trial. Children will be matched in pairs at baseline and randomly allocated to receive either 20 weeks of Mitii™ training (30 min per day, six days a week, with a potential total dose of 60 h) immediately, or be waitlisted for 20 weeks. Outcomes will be assessed at baseline, immediately post-intervention and at 20 weeks post-intervention. The primary outcomes will be the Assessment of Motor and Process Skills and 30 s repetition maximum of functional strength exercises (sit-to-stand, step-ups and half kneel to stand). Measures of body structure and functions, activity, participation and quality of life will assess the efficacy of Mitii™ across all domains of the International Classification of Functioning, Disability and Health framework. A subset of children will undertake three tesla (3T) magnetic resonance imaging scans to evaluate functional neurovascular changes, structural imaging, diffusion imaging and resting state functional connectivity before and after intervention.

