### Primary hypotheses

Compared to usual care, Mitii™ training will achieve significantly greater gains in:Activities of daily living motor processing skills as indicated by an improvement of a minimum detectable change (MDC) of 0.5 logit scores on the Assessment of Motor and Process Skills (AMPS) immediately following training;Gross motor capacity assessed by 30 s repetition maximum (rep_max_) of functional strength exercises (MDC = ≥28 repetitions on composite score of three functional strength exercises)

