### Lower Limb (LL) functional strength

Thirty second repetition maximum (rep_max_) of functional strength exercises (including sit-to-stand, lateral step-ups and half-kneel to stand) will be tested according to published recommendations [93]:

Sit-to-stand: This test measures the ability of the participant to attain standing (from 90° knee flexion) as many times as possible in 30 s with arms free or placed on their hips and without support from the chair or their body. Height of the chair will be defined by the ability of the participant to attain 90° hip and knee flexion with feet flat on the floor. One repetition will be defined as each time the participant is within 15° of hip and knee extension, visually estimated by a physiotherapist.

Lateral Step-Up: The aim of this test is to perform as many step up repetitions onto a 20 cm step block as possible in 30 s. Participants will be asked to stand with the foot being tested on the step and the non-test leg on the floor, parallel and shoulder width apart. The participant then raises the non-test foot off the ground until the test leg has reached within 10° of knee extension (visually estimated) for the tested foot during the extension phase of the test. The non-test foot does not have to touch the step block. Repetitions will be counted each time the heel or toes of the foot not being tested touches the ground. Both legs will be tested with the dominant leg tested first.

Half-kneel to Stand: This activity tests the ability of participants to attain a stride stance through a half-kneel position without the use of arms for as many repetitions that can be completed in 30 s. The participant is placed in half-kneel with buttocks clear of the lower legs and floor. The participant will be instructed to assume a standing position within 15° of knee extension (visually estimated) and remain with their feet apart (one repetition). This is a slight adaptation to the original protocol where participants assumed a standing position with feet together. The dominant leg in front will be tested first and repeated for the non-dominant side.

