For each LL functional strength exercise participants will be given verbal and visual instructions as well as two practice repetitions prior to testing. The exercises will be assessed in the following order: (i) Sit-to-stand, (ii) Lateral step-up dominant, (iii) Lateral step-up non-dominant, (iv) Half-kneel to stand dominant and (v) Half-kneel to stand non-dominant and participants will be given verbal encouragement throughout. Participants will be given 180 s rests between exercises. If a participant cannot complete an exercise whilst performing the practice attempts, they will be assigned a score of 0 and will not proceed to testing.

Functional strength tests demonstrate acceptable inter-tester reliability (ICC= > 0.91; coefficient of variation (CV) 12.1-22.7 %) in 25 children with CP [93]. Reliability for each of these three tests was also strong (Lateral step up ICC = 0.94; Sit to stand ICC = 0.91; Half kneel to stand ICC = 0.93-0.96) [93]. Mean repetitions for each of the functional measures were as follows: (i) sit-to-stand was 14.4 (SD = 5.0; Standard error of measurement [SEM] = 1.5 reps; CV = 12.1 %), (ii) lateral step up left were 13.2 (SD = 10.5; SEM = 2.4 reps; CV = 17.8 %), (iii) Lateral step-up right was 12.6 (SD = 10.4; SEM = 2.6 reps; CV = 22.7 %), (iv) Half-kneel to stand left was 7.5 (SD = 5.5; SEM = 1.1 reps; CV = 28.6 %), (v) Half-kneel to stand right was 6.0 (SD = 5.3; SEM = 1.4 reps; CV = 39.9 %) [93].

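### The 80 % power stated for the second primary outcome (26 per group) is calculated on sit-to-stand alone, while the hypothesis is on a composite of three exercises

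*Protocol article*

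**What the plan says.** The Abstract names as a primary outcome the "30 s repetition maximum of functional strength exercises (sit-to-stand, step-ups and half kneel to stand"). The Primary hypotheses section puts the hypothesis on a composite and attaches a threshold to it: "MDC = ≥28 repetitions on composite score of three functional strength exercises". The section on lower limb functional strength describes five 30 s tests, because step-up and half-kneel to stand are each done on both legs. It prints means and SDs for all five from a reliability study in children with cerebral palsy. The sit-to-stand SD there is 5.0. The step-up SDs are about twice that, for example "lateral step up left were 13.2 (SD = 10.5; SEM = 2.4 reps; CV = 17.8" %).

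The Sample size section opens with the power claim, which covers both primary outcomes: "The primary basis for sample size calculation for this study is adequate power (80 %) to detect a clinically important difference". For the strength outcome it then uses one SD, "the response within each subject group was normally distributed with a SD of five sit-to-stand repetitions", and one difference: "If the clinically important difference between groups is four repetitions we will need 26 children from each group to complete 20 week follow-up assessments". It gives no SD for the composite and does not mention the 28-repetition threshold. The protocol does not say how the composite is formed.

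**The concern.** The calculation is presented as the requirement for a primary outcome, but its SD belongs to one of the three exercises that make up that outcome. Its four-repetition difference stands beside that SD, while the hypothesis names 28 repetitions on the composite. A reader therefore cannot tell what difference the trial has 80 % power to detect on the variable it will test.

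This matters most if the result is null. The Background describes the sample as adequately powered. A non-significant composite result would be read against that claim, without anyone being able to say whether the design was meant to detect four repetitions or 28.

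**Working it through.** **Inputs.** From the Sample size section: SD 5, difference 4, α = 0.05, 80 % power, equal groups. From the functional strength section, the five SDs: sit-to-stand 5.0, step-up left 10.5 and right 10.4, half-kneel left 5.5 and right 5.3. From the Primary hypotheses: 28 repetitions. From the Abstract: 30 per group enrolled. α is taken as two-sided, which the protocol does not state.

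**Formula.** Two-sample t-test, noncentrality λ = Δ / (SD × √(2/n)), 2n − 2 degrees of freedom.

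**1. The protocol's own figure.** At n = 26, λ = 4 / (5 × 0.277) = 2.88, giving power 80.7 %. At n = 25 the power is 79.1 %. The stated 26 per group reproduces, for sit-to-stand.

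**2. SD of the composite.** The protocol gives neither a formula for the composite nor correlations between the tests. Assume an unweighted sum of the five tests with a common correlation r:

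- Sum of squared SDs: 25.00 + 110.25 + 108.16 + 30.25 + 28.09 = 301.75
- Sum of SDs: 36.7, which squared is 1346.89
- Variance = (1 − r) × 301.75 + r × 1346.89
- r = 0: SD = √301.75 = 17.4
- r = 0.5: SD = √824.32 = 28.7
- r = 1: SD = 36.7

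**3. Power on the five-test sum, unadjusted.**

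| Assumed r | SD | 28 reps, n = 26 | 28 reps, n = 30 | 4 reps, n = 26 | Detectable at 80 %, n = 30 |
|---|---|---|---|---|---|
| 0 | 17.4 | >99 % | >99 % | 13 % | 12.8 |
| 0.5 | 28.7 | 93 % | 96 % | 8 % | 21.1 |
| 1 | 36.7 | 77 % | 83 % | 7 % | 27.0 |

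Example (r = 1, n = 26, 28 repetitions): λ = 28 / (36.7 × 0.277) = 2.75, power 77 %. The normal approximation puts the lowest four-repetition figure at 6 % instead of 7 %.

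**4. Legs averaged instead of summed.** The step-up and half-kneel SDs are halved before summing: 5.0, 5.25, 5.2, 2.75, 2.65. The sum of squares is 94.19 and the sum is 20.85. The SD is 9.7, 16.3 or 20.85 for r = 0, 0.5 or 1. Power for 28 repetitions is over 99 % in every case, at 26 and at 30 per group.

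**The case against.** The strongest reply is that nothing in the trial depends on this paragraph. The 26 is computed correctly for its inputs. The other primary outcome, the AMPS, requires 29 per group and sets the planned 60. The only composite threshold in the protocol is 28 repetitions, and for that value the enrolled sample has 83 % power or more at every assumed correlation. The planned analysis also adjusts for the baseline score, which the working above ignores. If the baseline to 20-week correlation were 0.5 (an assumption; the protocol gives none), the least favourable SD would fall to 36.7 × √(1 − 0.25) = 31.8. Power for 28 repetitions would then be about 88 % at 26 per group and 92 % at 30.

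All of that stands, and it limits the point. A reader might infer from the mismatch, or from the 7 to 13 % figures, that the trial is underpowered for functional strength. The documents do not support that. Those low figures apply only if four repetitions is meant as the target on the whole composite, which the protocol does not say.

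What the reply does not remove is that the 80 % is stated for an outcome whose SD and threshold were not used to obtain it. The protocol labels 28 a minimum detectable change and does not adopt it as the sizing difference. Adequate power for 28 repetitions is therefore something a reader can work out under assumptions, not something the protocol states.

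**Conclusion.** The point holds as a mismatch between outcome and inputs, not as an arithmetic error. The stated 80 % at 26 per group applies to a four-repetition difference in sit-to-stand. It does not apply to the composite on which the primary hypothesis rests.

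For the composite, what the sample can detect depends on the target difference and on how the score is formed. On the five-test sum, power at 26 per group runs from 77 % to over 99 % for 28 repetitions, and is roughly 7 to 13 % for four. At 30 per group, the difference detectable with 80 % power is about 13 to 27 repetitions, which lies below 28 throughout.

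These ranges assume an unweighted composite, a common correlation between tests, SDs from children with cerebral palsy carried over to acquired brain injury, all enrolled children assessed at 20 weeks (for the figures at 30), and no gain from matching or baseline adjustment. The paragraph should be corrected, but the design does not depend on it.

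**What to change.** Rewrite the strength paragraph of the Sample size section on the composite:

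- Define how the composite is formed: sum of five tests, three exercises with legs averaged, or another rule.
- State its SD, or a range with the assumed correlation between tests.
- State one target between-group difference on that scale, and reconcile it with the 28 repetitions in the Primary hypotheses.
- Restate the power, or the detectable difference, at 30 per group. For an unweighted five-test sum this is about 13 to 27 repetitions at 80 % power, before any gain from the planned baseline adjustment.

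The sit-to-stand calculation can stay if it is labelled as such. Making sit-to-stand the primary score in order to keep the 26 is not advised, since it would change the hypothesis to preserve a number. The cost is one rewritten paragraph, with no added participants and no change to the primary outcome.
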